#### Control group

Subjects in the control group will use the WMD by themselves. They will not receive services from the CHWs and the research nurse unless abnormalities are detected by the WMD (e.g., abnormally high blood pressure), in which case the nurse will follow up on the subjects according to the protocols.

### Outcome measures

#### Usability

The aspect of the usability of the WMD includes facilitators and barriers to using the device, the level of satisfaction with the safety, convenience, and features of the device, attitude towards the use of the WMD, the perceived usefulness of the device and its perceived ease of use, and self-efficacy and level of anxiety in using the device. Subjects will be asked to take part in a focus group interview and provide feedback on the facilitators and barriers to using the device, and on their level of satisfaction with the safety, convenience, and features of the device. Attitudes on using the WMD, the perceived usefulness of the device and its perceived ease of use, self-efficacy, anxiety levels, and facilitating conditions in the use of the device will be measured using the senior technology acceptance model (STAM), which has been modified from a widely used and validated technology acceptance model. It measures using a 10-point Likert scale ranging from 1 (strongly disagree) to 10 (strongly agree). The higher the score, the better the outcome related to WMD usage. Anxiety level is the exception, where a higher score indicates greater anxiety [25,26].

#### Feasibility

The feasibility of this program will be evaluated by assessing the rate of recruitment, attrition rate, adverse events such as discomfort or injuries, and technical difficulties such as synchronization of the data from the WMD to the smartphone application. The data will be recorded by a designated staff member in each of the five centers. The rate of recruitment will be determined by dividing the number of eligible subjects who were recruited and randomized by the total number of eligible subjects. The rate of attrition will be calculated by dividing the number of subjects who quit or who could not be followed up by the total number of subjects who finished the program.

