### Study setting, subjects, and recruitment strategies

The recruitment will be carried out in five community centers. Members of the community centers who have shown an interest in this program will be screened and recruited. The inclusion criteria are: (1) 60 years old or older, (2) owning a smartphone, (3) able to communicate in Cantonese or Mandarin, and (4) able to access the internet. The exclusion criteria are: (1) having a medically diagnosed cognitive impairment, (2) being bedbound, (3) already own a WMD, and (4) involved in other WMD-related studies.

A research assistant will explain details of the study to the eligible subjects. The written consent of the participants and their baseline data will be collected at the community centers. The participants will be randomly assigned to either the intervention or control group using group assignments generated by the Research Randomizer software. The group assignments will be sealed and opened sequentially by the principal investigator at the time of randomization. To maximize the level of double-blinding, participants will be informed that the intervention aimed to promote the use of the WMDs but will not be informed about their specific assignment to the intervention or control group. Furthermore, the research assistant responsible for data collection will remain blinded to the group allocation, while the providers, including community center staff, will not be blinded.

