#### Intervention group

The subjects in the intervention group will receive a three-month program called Live With Wearable Monitoring Device (LWMD), which will be conducted by CHWs under the supervision of our research nurse. The nurse and the trained CHWs will provide a first home visit session to subjects in the first month. The nurse will use the Omaha System, an evidence-based and comprehensive tool widely used in community-based practice, to identify physical and psychosocial health problems among the subjects that could be prevented or resolved through the use of the WMD [22]. For instance, the nurse will assess ten problem areas of the Omaha System, utilizing functions such as blood pressure and pulse monitoring in the WMD. These problem areas include role change, interpersonal relationships, mental health, pain, respiration, sleep and rest patterns, circulation, physical activity, substance use, and medication regimen (Fig 2).

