**Fig 2 pone.0294517.g002:**
[figure not shown]
The problems of the Omaha System that linked with the blood pressure and pulse monitoring feature of the WMD.

In the event of abnormalities being detected, the nurse will suggest that participants utilize specific features of the WMD that are relevant to their identified health and social problems. They will provide recommendations regarding the duration and frequency of usage, as well as instructions on how to incorporate these features into their daily routines.

The CHWs will support the nurse with health assessments and the setting up of goals and action plans, and play an active role in communicating between the nurse and the subjects during the home visit. Starting from the third week, they will make regular phone calls to the subjects every other week until the twelfth week, to remind and encourage them to use the WMD. During the phone call, they will follow up on the problems that were identified by the nurse, on the subjects’ progress in attaining the goals, and suggest solutions for tackling the barriers preventing the subjects from implementing the action plans. The CHWs will seek help from the nurse when there is a need to modify the goals and action plan, or when any health issues arise that cannot be solved by the CHWs [23,24].

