### Data collection

The collection of data will occur at four time-points: baseline (T0), 1 month (T1), 3 months (T2), and 6 months (T3). T2 represents the immediate post-intervention period while T3 represents three months after the intervention for assessing the sustained effect of the program. At T0, baseline demographic data will be collected. Quantitative data will be collected at all four time-points through phone calls by the research assistant. Qualitative data will be collected at T2 through a semi-structured interview.

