### Data analysis

Statistical tests will be performed using the software, Statistical Package for Social Sciences (SPSS) version 26. Descriptive analyses will be used to present the baseline demographic data. The differences and changes in outcomes for the quantitative data will be estimated using the Generalized Estimating Equation (GEE). For each outcome, (1) the between the intervention and control group (between-group) effects, (2) the within-group (time) effects, and (3) the group-by-time interaction (group X time) effects will be investigated. However, it is important to note that the validity of the GEE analysis relies on the assumption that data are missing completely at random (MCAR) [31]. Therefore, we will employ Little’s test to assess whether the missing data in our dataset are MCAR. If the test results are significant or indicate non-MCAR data, we will utilize Weighted Generalized Estimating Equation (WGEE) to analyze the outcome measures instead. Intention-to-treat will be our primary choice to analyze the data [32]. The level of significance will be set at p < .05 for a two-tailed test.

The qualitative data from the semi-structured interviews will be examined using the principles of deductive thematic analysis [33]. All focus group interviews will be conducted with audio recordings. Transcription and translation will be performed manually by research team members. To enhance conformability, an audit trail will be maintained to resolve any differences through agreement.

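### Adverse events and technical difficulties are recorded by unblinded centre staff with no stated schedule for asking, while the intervention arm has six more scheduled contacts, so recorded counts may be incomplete and may differ by arm

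*Protocol article*

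**What the plan says.** All places are in the protocol article.

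- **Outcomes.** The second objective and the Feasibility section name four items: recruitment, attrition, "adverse events such as discomfort or injuries, and technical difficulties such as synchronization of the data from the WMD to the smartphone application".
- **Recorder.** For these items the Feasibility section states: "The data will be recorded by a designated staff member in each of the five centers".
- **Blinding.** The section on setting, subjects and recruitment says that "the research assistant responsible for data collection will remain blinded to the group allocation", whereas "the providers, including community center staff, will not be blinded".
- **Contacts in the intervention arm only.** Under Intervention group: "The nurse and the trained CHWs will provide a first home visit session to subjects in the first month". From the third week, the CHWs also act as follows: "they will make regular phone calls to the subjects every other week until the twelfth week". The calls cover the problems the nurse identified, progress towards goals, and barriers to the action plan.
- **Control arm.** Controls get no CHW or nurse service unless the device detects an abnormality.
- **Contacts in both arms.** Under Data collection: "Quantitative data will be collected at all four time-points through phone calls by the research assistant". Both arms also have the same training session, a hotline number left at the centre, and nurse follow-up of abnormal readings.
- **Analysis.** After introducing generalized estimating equations for the quantitative data, the Data analysis section says: "For each outcome, (1) the between the intervention and control group (between-group) effects", together with time and interaction effects, will be investigated.

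**The concern.** Two stated choices combine badly. The article gives adverse events and technical difficulties to a recorder who is not blinded, although a blinded data collector already phones every participant. It also gives one arm many more occasions on which a problem can come up. Device discomfort or a failed synchronization need not trigger an abnormal-reading alert. For a control participant, such a problem may reach the centre record only if the participant volunteers it.

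At stake are two of the four feasibility outcomes. If capture is incomplete, the overall rates are too low. If it is less complete in controls, the program could look more trouble-prone than device-only use merely because its participants are in closer contact. Even if the counts are only described by arm, readers will compare them.

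**Working it through.** The plan states no event rate or capture rate, so it has no figure of its own to reproduce on this point. Two things can be worked out: the number of scheduled contacts by arm, and how an apparent difference would depend on capture.

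**1. Scheduled contacts after baseline**

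Inputs: research assistant calls at 1, 3 and 6 months (Data collection); one home visit in the first month, and CHW calls every other week from week 3 until week 12 (Intervention group).

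- CHW calls: weeks 3, 5, 7, 9, 11 = 5.
- Contacts in the intervention arm only: 1 visit + 5 calls = 6.

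| Period | Intervention | Control |
|---|---|---|
| To month 3 | 2 + 6 = 8 | 2 |
| To month 6 | 3 + 6 = 9 | 3 |

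The whole imbalance falls in the first three months. From then to month 6 each arm has one scheduled contact.

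**2. Which contacts feed the record**

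The Feasibility section names the recorder but not the source of the information. The article does not say whether the research assistant's calls ask about these items, or whether CHW and nurse reports reach the designated staff member. That leaves three possibilities:

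- The calls ask, and their answers supply the rates: 3 contacts against 3, and no imbalance. The Feasibility section then names a different recorder from the one who collects the data.
- The calls do not ask, and CHW or nurse reports are passed on: the intervention arm has up to six further routes into the record, and controls have none of these.
- The calls do not ask, and CHW or nurse reports are not passed on: the arms are more alike, but problems heard in those contacts are lost and the overall counts are too low.

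**3. Illustration only**

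Assume 35 per arm (from the Sample size section), the same true event proportion p in both arms, and capture proportions cI (intervention) and cC (control). The values of p, cI and cC are assumptions and do not come from the document.

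Expected recorded events = 35 × p × c. Apparent risk ratio = cI / cC, whatever the value of p.

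With p = 0.20:

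| cI | cC | Intervention | Control | Apparent ratio |
|---|---|---|---|---|
| 0.90 | 0.90 | 6.3 | 6.3 | 1.0 |
| 0.90 | 0.70 | 6.3 | 4.9 | 1.29 |
| 0.90 | 0.50 | 6.3 | 3.5 | 1.8 |
| 0.90 | 0.30 | 6.3 | 2.1 | 3.0 |
| 0.80 | 0.60 | 5.6 | 4.2 | 1.33 |
| 0.80 | 0.40 | 5.6 | 2.8 | 2.0 |

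For overall understatement, take the third row: (6.3 + 3.5) / 70 = 14% recorded against a true 20%.

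The ratio is simply one assumed capture proportion divided by the other. The table shows how sensitive the counts are to unequal capture; it does not estimate what this trial would see.

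**The case against.** The strongest reply is that the article says who records the data and not how events are elicited, and that a condensed article may leave elicitation to the full protocol. That stands as far as the missing script goes, and silence about forms or frequency is not the point raised here. The point is about what is stated: an unblinded recorder is named although a blinded collector is available, and only one arm has the extra contacts.

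Four further replies have force:

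- **Controls are not without contact.** A reader might infer that they have none. The Data collection section contradicts this: both arms have blinded calls, and these may already ask about the two items. Only the centre staff have no stated schedule.
- **Unequal capture is not shown.** A reader might infer that capture does differ by arm. The document supports a risk only. The CHW calls are not described as an adverse-event enquiry. CHWs refer matters to the nurse, and no link from CHW or nurse to the centre recorder is described.
- **Other routes cover both arms.** The hotline, nurse follow-up of abnormal readings, self-reported attendances confirmed by certificates, and focus groups apply to both arms. Injuries leading to care should show among the attendances. Discomfort and synchronization problems would be less likely to.
- **A between-arm test of these counts is doubtful.** The phrase about each outcome follows a sentence on repeated quantitative measures. It cannot literally cover every feasibility item, since the recruitment rate is fixed at randomization. The concern therefore does not rest on a planned test.

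**Conclusion.** The concern holds as a risk arising from stated choices, not as a demonstrated bias. What is established is an unblinded recorder, no stated schedule for that recorder to ask, and 9 scheduled contacts after baseline against 3 over six months (8 against 2 in the first three). It follows that the counts of adverse events and technical difficulties may be incomplete and may differ by arm for reasons unrelated to the program.

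The size cannot be derived from the document. An apparent ratio anywhere from 1.0 to 3.0 follows from the assumed capture proportions above, and none of these values should be quoted as an expected effect. If the research assistant's calls already supply these items, the imbalance disappears and what remains is an inconsistency about who records them. The case for change rests mainly on how little it costs to remove the doubt.

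**What to change.** Have the blinded research assistant ask every participant the same short adverse-event and technical-difficulty questions at the T1, T2 and T3 calls. Use those answers as the source for the feasibility rates by arm, so that 3 contacts against 3 feed the record. Keep reports from centre staff, CHWs, the nurse and the hotline as a supplementary log, reported separately by source.

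If the calls already include such questions, say so and reconcile the Feasibility section with the Data collection section, so that one source and one recorder are named for these outcomes.

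The cost is two or three scripted questions in existing calls, with no extra staff or visits. The calls become slightly longer, and reported event counts will probably rise because participants are asked directly. The calls are up to three months apart, so minor events may still be forgotten, but both arms would be asked over the same intervals.

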Compared with healthcare providers, CHWs are more familiar with the older adults and have more free time to teach them how to use the health features of the WMD and to overcome technical difficulties. There is, however, no study evaluating the effectiveness of CHW-led intervention programs on the sustained use of technological devices, including WMD, among community-dwelling older adults. In a pilot study in India, a training program was designed for CHWs to promote the use of WMDs to the public, but there was no data on the rates of usage and adherence [20]. The Live With Wearable Monitoring Device (LWMD) program is the first to integrate a peer support model to motivate older adults to sustain their use of a WMD for health monitoring and self-care management. This new approach has the potential to encourage the older adults to prolong and sustain their use of the device, thereby improving their long-term health and quality of life, and reducing their use of tertiary healthcare services.

There are three objectives in this study:

Assess the usability of the WMD from the perspective of older adults, including facilitators and barriers to the use of the device, level of satisfaction with the safety, convenience, and features of the device, attitude towards the use of the device, the perceived usefulness of the device, its perceived ease of use, and self-efficacy and level of anxiety in using the device.Evaluate the feasibility of the Live With Wearable Monitoring Device program, including the recruitment rate, attrition rate, adverse events, and technical difficulties.Identify the preliminary effectiveness of the LWMD program among older adults dwelling in the community, including their quality of life, utilization of health services, sustained use intention, and rate of adherence.

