### Sample size

A power analysis was used to calculate the sample size for this study. We adopted usability as our primary outcome measure. To determine the effect size for our study, we referred to the Overall Acceptability Score [34], where the intervention group scored 45.2 (2.9) and the control group scored 40.4 (1.3). To account for potential differences in our local sample, which may consist of older individuals with lower mobile device literacy, we used a conservative approach and discounted the effect size by one-third for sample size calculation (which was 0.72). This was done to ensure an adequate sample size.

Assuming an alpha value of 0.05, a power of 80%, and an effect size of 0.72 [33], the sample size for each group should be 32. Accounting for a 10% drop-out rate, the total sample size in this study will be 70 (i.e., 35 per group).

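### The attrition rate is defined as losses divided by completers instead of by subjects randomised, which overstates it, and the time-point for finishing is not fixed.

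*Protocol article*

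**What the plan says.** The objectives at the end of the Introduction describe the feasibility evaluation as "including the recruitment rate, attrition rate, adverse events, and technical difficulties". The Feasibility section under Outcome measures then gives formulas for two of these. The recruitment rate comes from "dividing the number of eligible subjects who were recruited and randomized by the total number of eligible subjects". The attrition rate comes from "dividing the number of subjects who quit or who could not be followed up by the total number of subjects who finished the program". Nothing elsewhere in the article restates or corrects the attrition formula.

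The number to be randomised is given under Sample size: "Accounting for a 10% drop-out rate, the total sample size in this study will be 70 (i.e., 35 per group"). The Intervention group section describes a three-month program. The Data collection section places T2 at 3 months, directly after the intervention, and T3 at 6 months.

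**The concern.** A rate of attrition normally answers the question: of those who entered the trial, what share was lost? Everyone in the numerator then belongs to the denominator. The recruitment rate in the same section is built that way, with those randomised taken as a share of all eligible. The attrition rate is not. Its denominator is the subjects who finished, so those who were lost are taken out of the base against which they are counted.

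This is more than a detail left to a fuller document, because the article fixes a formula and the formula is wrong. Attrition is one of the four named components of the feasibility objective. A reader who sees it reported as a percentage will take it as a share of those randomised and compare it with attrition elsewhere on that basis. If someone later used the figure to plan another study (an assumption, as the article plans none), an odds entered as a proportion would over-inflate that sample size.

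**Working it through.** **Inputs**
- Attrition formula: Feasibility section, as quoted.
- Number randomised, N = 70 (35 per group): Sample size section.
- Program end at 3 months (T2) and last follow-up at 6 months (T3): Intervention group and Data collection sections.
- Number lost, D: an outcome, so not in the article. The values below are illustrations.

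**Step 1: the plan's own figure.** The article states no attrition figure, so there is none to reproduce. The sample size on which N rests does reproduce: a two-sample t-test with effect size 0.72, two-sided alpha 0.05 and 80% power needs 31.27 per group, rounded up to the stated 32. The plan then sets 35 per group, so N = 70.

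**Step 2: every subject either finishes or is lost.** Finishers number N − D. With p = D/N, the stated formula gives

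D/(N − D) = p/(1 − p),

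which is the odds of loss. It exceeds p by the factor 1/(1 − p), and the two agree only when D = 0.

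| Lost, D | Stated formula, D/(70 − D) | Share of randomised, D/70 | Ratio |
|---|---|---|---|
| 7 | 7/63 = 11.1% | 10.0% | 1.11 |
| 14 | 14/56 = 25.0% | 20.0% | 1.25 |
| 21 | 21/49 = 42.9% | 30.0% | 1.43 |
| 36 | 36/34 = 105.9% | 51.4% | 2.06 |

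**Step 3: finishing read as reaching T2.** Let D1 be the number lost before T2 and D2 the number lost between T2 and T3. Finishers are then N − D1, and the D2 subjects are in both counts. The formula gives (D1 + D2)/(N − D1). With 14 lost in all:
- all before T2: 14/56 = 25.0%
- 7 before and 7 after: 14/63 = 22.2%
- all after T2: 14/70 = 20.0%

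The share of those randomised is 14/70 = 20.0% in each case. On this reading the overstatement depends on when the losses occur and disappears if none occurs before T2. The same total loss can therefore produce different reported rates.

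**The case against.** The strongest reply is that the consequence is small. At 7 of 70 lost, the two calculations differ by 1.1 percentage points. No threshold or progression rule is attached to attrition, and a reader given the number randomised and the number lost can recompute the proportion. If finishing means reaching T2, the figures in the table are upper limits for a given number lost. All of this stands and limits the severity. It does not make the formula right.

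Three stronger readings are tempting, and the article does not support them.

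- **That the reported rate cannot be compared with the planned drop-out.** The Sample size section says only "Accounting for a 10% drop-out rate" and does not name the base. As a share of those enrolled, 32/0.90 = 35.6, which rounds up to 36 per group. As an addition to the completers needed, 32 × 1.10 = 35.2, which is closer to the stated 35. A mismatch of scale between the two figures cannot be shown.
- **That control losses would be divided by intervention-arm completers.** A reader might argue this because "Subjects in the control group will use the WMD by themselves" and so have no program to finish. With 7 lost overall and about 31.5 intervention completers (35 × 0.90), that would give 7/31.5 = 22%. But the article also uses the word program for the study as a whole: in the recruitment section, before randomisation, and in the Intervention section where it describes the nurse's follow-up of all subjects. Finishing the study is the more natural meaning, and the 22% should not be relied on.
- **That the rate is likely to exceed 100%.** This needs at least 36 of 70 lost. The high discontinuation figures cited in the Introduction concern people who stopped using a device, which is not the same as loss from a trial.

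**Conclusion.** The point holds. The stated formula divides by the wrong group, and following it misreports a named feasibility outcome. If every subject either finishes or is lost, and all 70 planned subjects are randomised, the overstatement is 1.1 percentage points at 7 lost, 5 at 14 lost and 12.9 at 21 lost. It is smaller if finishing means reaching T2 and some losses fall between T2 and T3. The missing time-point is a second, separate defect in the same sentence.

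The sample size, the power and the GEE analyses of effectiveness do not use this rate and are unaffected. This is a minor to moderate correction.

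**What to change.** Replace the attrition sentence in the Feasibility section with a definition along these lines: the attrition rate is the number of randomised subjects who withdrew or were lost to follow-up by T3 (6 months), divided by the number randomised, given overall (planned denominator 70) and for each arm (planned denominator 35). This fixes the denominator and the time-point together.

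The cost is one sentence. The required counts are already to be recorded at the five centers, and no change to the sample size or the effectiveness analysis follows. If data collection has finished, the correction can be made at reporting, with the change of definition stated.
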